## Abstract

**Background:**

About 1.35 million deaths annually are attributed to tobacco use in India. The main challenge, given the magnitude of tobacco use and limited resources, is delivering cessation support at scale, low cost, and through a coordinated cross-system effort; one such example being brief advice interventions. However, highly credentialed staff to identify and counsel tobacco users are scarce. Task-shifting is an important opportunity for scaling these interventions.

**Objective:**

The LifeFirst SWASTH (Supporting Wellbeing among Adults by Stopping Tobacco Habit) program—adapted from the LifeFirst program (developed by the Narotam Sekhsaria Foundation, Mumbai, India)—is a tobacco cessation program focusing on lower-socioeconomic status patients in Mumbai receiving private health care. This parallel-arm, cluster randomized controlled trial investigates whether the LifeFirst SWASTH program increases tobacco cessation rates in low-resource, high-reach health care settings in Mumbai.

**Methods:**

This study will target tuberculosis-specific nongovernmental organizations (NGOs), dental clinics, and NGOs implementing general health programs serving lower-socioeconomic status patients. Intervention arm patients will receive a pamphlet explaining tobacco’s harmful effects. Practitioners will be trained to deliver brief cessation advice, and interested patients will be referred to a Narotam Sekhsaria Foundation counselor for free telephone counseling for 6 months. Control arm patients will receive the same pamphlet but not brief advice or counseling. Practitioners will have a customized mobile app to facilitate intervention delivery. Practitioners will also have access to a peer network through WhatsApp. The primary outcome is a 30-day point prevalence abstinence from tobacco. Secondary outcomes for patients and practitioners relate to intervention implementation.

**Results:**

The study was funded in June 2020. Due to the COVID-19 pandemic, the study experienced some delays, and practitioner recruitment commenced in November 2023. As of July 2024, all practitioners have been recruited, and practitioner recruitment and training are complete. Furthermore, 36% (1687/4688) of patients have been recruited.

**Conclusions:**

It is hypothesized that those patients who participated in the LifeFirst SWASTH program will be more likely to have been abstinent from tobacco for 30 consecutive days by the end of 6 months or at least decreased their tobacco use. LifeFirst SWASTH, if found to be effective in terms of cessation outcomes and implementation, has the potential to be scaled to other settings in India and other low- and middle-income countries. The study will be conducted in low-resource settings and will reach many patients, which will increase the impact if scaled. It will use task-shifting and an app that can be tailored to different settings, also enabling scalability. Findings will build the literature for translating evidence-based interventions from high-income countries to low- and middle-income countries and from high- to low-resource settings.

**Trial Registration:**

ClinicalTrials.gov NCT05234983; https://clinicaltrials.gov/study/NCT05234983

**International Registered Report Identifier (IRRID):**

DERR1-10.2196/57236

### Barriers to Scaling Up Evidence-Based Tobacco Cessation in India

Low-resource settings require tobacco cessation evidence-based interventions (EBIs) that can be delivered, sustained, and scaled up at low cost [6-8]. However, tobacco cessation EBIs typically include pharmacotherapy, a resource still beyond the reach of most tobacco users and many health care systems in India [9], even though a limited number of pharmacotherapeutic treatments were recently added to the Indian Ministry of Health and Family Welfare’s List of Essential Medicines [10]. Also, most tobacco cessation EBIs focus solely on cigarette smoking, which is a mismatch for India given the high rates of smokeless and dual tobacco use [11], and the fact that the smokeless tobacco market in India is the largest in the world [12]. Additionally, EBIs are more likely to be scaled up in low- and middle-income countries (LMICs) if they are simple and inexpensive and can be delivered via alternative channels, such as NGOs or small private practices, rather than relying entirely on government infrastructure and highly skilled personnel [13]. Finally, there is an overall lack of effective interventions to support health care practitioners in implementing evidence-based practices across various health topics in LMICs [14].

### Brief Advice Interventions

One type of low-cost, scalable cessation support is brief advice interventions, or short engagement by health care providers to screen for tobacco use, offer brief cessation advice, and refer users to treatment resources [15]. Brief advice interventions are effective for both smoked and smokeless tobacco [16,17]. However, according to the GATS-2 in India, only 49.6% (37,332/76,500), of smokers and 31.7% (24,251/76,500) of smokeless tobacco users were advised to quit by a health care provider [2], highlighting a potential role for brief advice interventions [18].

### Task-Shifting: Benefits and Training Requirements

The use of diverse health professionals (rather than only highly credentialed individuals) is an important opportunity for brief advice interventions [9]. India meets only 25% of the WHO benchmark for health care staffing, and the available educational facilities are insufficient to grow the workforce to needed levels [19]. To reach the needed staffing levels, the number of physicians would need to increase by 151%, but the current annual growth rate is 10%-14% [20]. Task-shifting is a strategy that emphasizes moving tasks from highly credentialed workers to less credentialed (but more readily available) workers and can promote access to preventive services and health. The task-shifting model has been effectively used to deliver mental health EBIs in LMICs, showing that health care providers with little or no prior mental health training, and often little formal education, can deliver EBIs effectively with positive clinical outcomes [21]. An important consideration for task-shifting models is the changes needed to adapt practitioner training to meet the needs of practitioners who have fewer formal credentials. For example, an EBI for autism spectrum disorder was adapted from the United Kingdom to sites in India and Pakistan. The use of nonspecialists to deliver the program necessitated a change from a 2-day training for therapists to a 4-week training for nonspecialists and new referral patterns and measures for nonspecialist competencies [22]. Another study trained community health workers (CHWs) in Tamil Nadu, India, to screen, examine, refer to further care, and follow up with patients with diabetes with the support of a tablet-based app. The CHWs were successful in their efforts compared to usual care, further indicating the use of task-shifting [23] The specific question addressed by this study is whether brief advice interventions can be delivered by a diverse range of health professionals instead of highly trained counselors.

### Delivering Sufficient Training Dose Using Technology

Practitioner training is a critical driver of program success [24,25] and can increase practitioners’ knowledge, skills, motivation, and ability to implement EBIs [25-30]. Successful training requires spending enough time (achieving sufficient dose) and offering supports (such as ongoing technical assistance), connections, and resources, a challenge in low-resource settings [29]. Communication technologies, such as mobile phones, offer a tremendous opportunity and have been used with frontline health workers to increase knowledge and skills, deliver learning materials and reminders, improve guideline adherence, increase patient follow-up rates, increase worker credibility in the community, and support knowledge generation [31-34]

### The Current Intervention

Narotam Sekhsaria Foundation (NSF) is an organization that has been working on tobacco cessation programs at various sites in the Mumbai Metropolitan Region (MMR) in India for more than 10 years. The NSF team developed and implemented LifeFirst, an evidence-informed tobacco cessation program involving cessation service provision in multiple settings including hospitals, workplaces, and schools, and conducting training for health care providers. It is based on EBIs developed in North America and Europe using the 5A’s framework [35-38]. The 5A’s framework (Ask, Advise, Assess, Assist, and Arrange) is a tool to help practitioners identify tobacco users, advise quitting, assess their readiness to quit, help them develop a plan, and arrange a follow-up visit or consultation [39]. The training builds skills and motivation to offer brief advice routinely and has two tiers: (1) a sensitizing version that orients practitioners to the need for tobacco control and builds skills for brief advice (Level 1) and (2) an intensive version to support practitioners in tobacco cessation counseling (Level 2).

The NSF team recently delivered the Level 1 training to 2000 practitioners. Before this, most participants had not received training to screen clients for tobacco use (83% or 1660/2000) or to provide cessation counseling (86% or 1720/2000). After receiving the training, participants reported increased knowledge to support patients and improved self-efficacy for counseling. Additionally, the team recently delivered the Level 2 training to 600 diverse health care providers from private and public hospitals, private practices, public health departments, and NGOs in Mumbai. Recently, NSF identified the potential for NGOs working on tuberculosis (TB) and treatment to deliver tobacco cessation, along with a need for less intensive interventions, setting the stage to test a brief intervention that requires few resources to implement [40].

The LifeFirst program has been adapted to develop LifeFirst Supporting Wellbeing among Adults by Stopping Tobacco Habit (SWASTH), which focuses on lower-socioeconomic status (SES) communities in Mumbai who receive health care through private dental practices and NGOs, including those working with TB patients (ClinicalTrials.gov NCT05234983). (“Swasth” means “healthy” in Hindi.) It is an EBI that involves training health care practitioners who serve lower-SES communities to ask their patients about tobacco use during health-related encounters, advise users to quit, and refer users willing to receive cessation support to LifeFirst SWASTH for 6 months’ cessation counseling. Counseling will be conducted by trained NSF staff counselors. The practitioners and counselors will use a customized mobile app to facilitate intervention delivery. Practitioners will also have access to a peer network through the social media platform WhatsApp, which will enable them to problem-solve together and enhance their capacity to implement EBIs in their clinics or practices.

### Objectives

Our objectives are as follows:

Aim 1: adapt the LifeFirst program and pilot-test LifeFirst SWASTH in 3 low-resource, high-reach settings: NGOs implementing general health programs, TB-specific NGOs, and dental clinics.Aim 2: conduct a cluster randomized controlled trial (RCT) to assess whether the adapted brief advice program results in increased cessation rates among tobacco users (compared to receiving a pamphlet explaining the health effects of tobacco use) in the aforementioned 3 types of low-resource, high-reach health care settings in Mumbai.Aim 3: evaluate the use of communication technologies, such as social media and an app, to support ongoing training and networking among practitioners in the intervention arm.

Our main focus in this paper is on effectiveness outcomes and will report more robustly on our exploratory implementation findings in the future.

### Theoretical Framework

The objective of this study is to test the effect of an adapted EBI, LifeFirst SWASTH, compared to receiving a pamphlet about the health effects of tobacco use, on improving cessation rates among tobacco users in 3 types of low-resource, high-reach health care settings in Mumbai: NGOs implementing general health programs, TB-specific NGOs, and dental clinics. This Hybrid Randomized Control Trial Type 1 study [41] will evaluate program effectiveness and explore the implementation of LifeFirst SWASTH, drawing on the US Public Health Service 5A’s model of tobacco control [42] and the Exploration, Preparation, Implementation Sustainment framework [24]. Figure 1 details the study’s theoretical framework. We hypothesize that 30-day point prevalence abstinence (PPA) will increase, and tobacco use will decrease at 6-month follow-up among patients in the adapted EBI, LifeFirst SWASTH, arm compared to the patients in the control arm.

**Figure 1 figure1:**
[figure not shown]
Theoretical framework supporting a hybrid effectiveness and implementation study. EBI: evidence-based intervention; NSF: Narotam Sekhsaria Foundation.

## Methods

### Design Overview

This study is a parallel-arm cluster RCT. Textbox 1 outlines the eligibility criteria for study sites. Textbox 2 details the participant eligibility criteria for practitioners and patients. Figure 2 provides an overview of the intervention design and flow.

Site eligibility criteria.Private (separate from the public or government-run health care system) nongovernmental organizations implementing general health programs, tuberculosis nongovernmental organizations, or dental practiceServes lower-socioeconomic status patientsLocated in the Mumbai Metropolitan RegionHas not previously received LifeFirst counseling training (Level 2)Is not currently running a tobacco cessation program

Participant eligibility criteria.
**Practitioner eligibility (n=132)**
Is aged 18 years and olderIs a targeted worker from a targeted setting (an outreach worker in a nongovernmental organization implementing general health programs, a community health worker in a tuberculosis-specific nongovernmental organization, or a dentist in private practice)Sees lower-socioeconomic status patientsHas sufficient language proficiency in English and/or Hindi to attend the training and take surveys, and have sufficient language proficiency in Hindi and/or Marathi to interface with patientsHas not received prior training in tobacco cessation counselingCan recruit 10-60 tobacco users in a 6-month periodWorks in a setting in which brief advice can be added to the workflowDelivers care in the Mumbai Metropolitan Region and expects to continue doing so for 1 year after completing the Supporting Wellbeing among Adults by Stopping Tobacco Habit practitioner trainingCan secure institutional signoff to participate and use the program in practiceHas an Android smartphone
**Patient eligibility (n=4688)**
Has used smokeless or smoked tobacco even once in the past 30 daysIs aged 18 years and overSpeaks Hindi or MarathiAttends the practice of an enrolled practitionerHas a mobile phone (required for data collection)Does not have another member of their household participating in the studyIs not currently participating in any tobacco cessation program (such as through the National Quitline)

**Figure 2 figure2:**
[figure not shown]
CONSORT (Consolidated Standards of Reporting Trials) flow diagram. LifeFirst SWASTH: LifeFirst Supporting Wellbeing among Adults by Stopping Tobacco Habit.

### Recruitment and Retention

The NSF team has rich experience in recruiting practitioners who meet these criteria and is already working with practitioners and leaders in each of the 3 practice settings in Mumbai. The team will leverage these connections to recruit a diverse pool of sites and practitioners. Additionally, all practitioners and patients in both the intervention and control arms will receive nominal monetary incentives for their time and effort. Participating NGOs will also receive nominal monetary incentives at the site level. As private dental practices are run by dentists (who are, in this case, practitioners), they will not receive an additional site-level incentive.

### Randomization

Sites will be randomized to conditions using random number generators in the SAS (version 9.4; SAS Institute). To ensure equivalence across treatment conditions, we will stratify random assignment based on two factors: (1) clinic types (eg, TB-specific NGOs, dental clinics, and NGOs implementing general health programs); (2) size of clinics with respect to the numbers of health care providers and patients. Randomization will be conducted within clinic types and matched by clinics with similar sizes. We will check the balance of treatment assignment on these 2 factors to assess the result of the random assignment. The health care providers and patients will not be blinded to their intervention condition.

A parallel study design will be used [43]. This design is considered the gold standard in assessing unbiased treatment effects given that randomization helps mitigate bias from known and unknown confounders. After randomization, individuals in each arm will stay in their assigned condition for the duration of the study. A cluster parallel RCT has the advantage of preventing inadvertent exposure to intervention or cross-over, thus reducing the risk of contamination [43].

### Intervention Arm

In LifeFirst SWASTH, patients who use tobacco will receive a pamphlet in Hindi about the harmful effects of tobacco. Practitioners will be trained to deliver the brief advice intervention. They will use an app to facilitate ongoing engagement and learning related to the adapted brief advice intervention. The app offers:

(1) a system to document patients’ tobacco use and refer them to LifeFirst SWASTH for counseling; (2) a dashboard allowing them to follow the progress of the patients they have referred; and (3) a repository of training materials and additional resources, for example, support material for promoting cessation, and quiz questions to test their knowledge.

An NSF-moderated group chat in the popular social media channel, WhatsApp, will also be used as a forum to share practitioners’ innovations and successes.

Within 15 days of referral, patients will be contacted by a trained NSF counselor over the telephone, given more details about the study, and asked whether they would like to provide informed consent and participate. The counselors will follow up with the patients for a total period of 6 months, with 4 specific follow-up intervals at 1 week, 1 month, 3 months, and 6 months after the initial detailed counseling call to ask about tobacco use and provide continued support.

### Control Arm

Patients in the control arm will be asked about tobacco use and will receive the same pamphlet as the intervention arm about the harmful effects of tobacco. Patients interested in participating in the study will be referred by practitioners to LifeFirst SWASTH. They will be contacted by NSF data collectors (who are not trained in counseling) over the telephone at the same 4 follow-up intervals as the intervention arm patients but will only be asked about their tobacco use status (this will be presented as NSF assessing the tobacco cessation landscape in MMR). During the RCT, if control patients request counseling, they will be referred to the NSF's regular programmatic counselors and withdrawn from the study. They will subsequently be assigned to the lost-to-follow-up group (due to requesting counseling). After their final follow-up, those control arm patients who have not quit will be offered LifeFirst counseling by NSF staff through the regular counseling program, separate from the study.

Like intervention arm practitioners, practitioners in the control arm will use an app to document patients’ tobacco use and register patients to be followed up by NSF. However, they will not be trained on the harms of tobacco use or advising tobacco-using patients on quitting and referring them to counseling. They will also not be part of a WhatsApp peer network. The training for control arm practitioners will emphasize that all patients will be given the option to access the intervention, including counseling, after their final follow-up with NSF. The control arm practitioners will also be offered the opportunity to receive the training after data collection is complete.

### Primary Outcome: Intervention Effectiveness

The primary outcome is a 30-day PPA from tobacco. Twenty percent of those who self-report tobacco cessation 6 months post recruitment will receive a cotinine test (using a urine sample) to biochemically verify abstinence.

### Secondary Outcomes

#### Patients

The secondary outcomes for patients are quit attempts, reduction in tobacco use, and psychosocial antecedents of behavior change such as knowledge, attitudes, and perceptions regarding the use of smoked or smokeless tobacco. These questions are primarily drawn from the GATS-2 survey, which was standardized, pretested in the field, and validated before being executed throughout India [2]. For the intervention arm patients, the survey includes questions regarding plans to quit and whether they have accessed other supports to do so, which will be tracked over time to assess the patient’s progress and readiness to quit.

#### Practitioners

The secondary outcomes for practitioners are knowledge, appropriateness, feasibility, acceptability, motivation to implement the intervention, and intervention delivery skills. The appropriateness, feasibility, and acceptability questions were adapted from the Intervention Appropriateness Measure, Feasibility of Intervention Measure, and Acceptability of Intervention Measure [44]. The original measures were validated thoroughly by Weiner and colleagues and demonstrated substantive and discriminant content validity [44]. We recognize that the populations with which the original validation studies were conducted are dissimilar from our practitioner groups, and thus will conduct cognitive testing of the items. Some questions, such as those measuring knowledge, are standard questions the NSF team uses for their LifeFirst training.

#### Counselors

The secondary outcomes for counselors will be the appropriateness, feasibility, and acceptability of the intervention. This information will be documented by the NSF team, as the counselors are NSF staff members.

### Data Collection and Analysis or Statistical Considerations

We will first examine the demographic characteristics of the intervention and control arms to verify that randomization has resulted in arms with similar baseline characteristics. Analyses will be based on intent-to-treat. To control for potential confounders identified in bivariate analyses, as well as variables of a priori clinical significance (SES, gender, age), we will regress the 6-month follow-up outcomes on the intervention status with the adjustment of baseline measures. We will use a regression model with a logit link function for binary outcomes (eg, tobacco cessation as our primary outcome), an identity link function for continuous outcomes (eg, number of cigarettes), and a Poisson link function for count outcomes (eg, number of attempts to quit). We will use robust standard error estimates (Generalized Estimating Equations method), adjusting for the clustering of patients among practitioners. We will conduct stratified analyses by clinic types to assess potential effect modification by settings. Independent variables with strong high correlations may result in collinearity. To assess the extent of collinearity, we will assess variance inflation factors and the standard error estimates for the adjusted model.

We will also measure the receipt of intervention using process data from the NSF team and conduct a dose-response analysis of the program impact. We will categorize patients in the intervention arm into 6 subgroups (brief advice, brief advice + intake, brief advice + intake + 1 follow-up, brief advice + intake + 2 follow-ups, etc). The mobile app will capture this information. While the study is not powered to detect differences between the subgroups definitively, we expect to be able to detect trends in response to the level of receipt of intervention, contingent on the distribution of exposure across subgroups.

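### The primary model chooses covariates partly by bivariate screening and does not name the randomisation factors, clinic type and size; a prespecified model including them would remove discretion and may gain precision

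*Protocol article*

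**What the plan says.** Under Randomization, the protocol article states that "we will stratify random assignment based on two factors: (1) clinic types", the second factor being "size of clinics with respect to the numbers of health care providers and patients". It adds: "Randomization will be conducted within clinic types and matched by clinics with similar sizes". The only later use given there for these two factors is a check of balance.

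Under Data Collection and Analysis or Statistical Considerations, the arms are first compared at baseline to "verify that randomization has resulted in arms with similar baseline characteristics". The covariate rule follows: "To control for potential confounders identified in bivariate analyses, as well as variables of a priori clinical significance (SES, gender, age"), and then "we will regress the 6-month follow-up outcomes on the intervention status with the adjustment of baseline measures". The primary outcome uses "a regression model with a logit link function for binary outcomes (eg, tobacco cessation as our primary outcome"). On variance: "We will use robust standard error estimates (Generalized Estimating Equations method), adjusting for the clustering of patients among practitioners". Clinic type appears in this section only as the basis of stratified analyses for effect modification. Clinic size does not appear in it.

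**The concern.** Two features of the stated rule can be improved.

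1. **Screening.** Part of the covariate set is found in the trial data. The text does not say whether the bivariate analyses look at association with arm, with outcome or with both. It gives no candidate variables and no threshold. An adjusted odds ratio depends in principle on the covariates in the model, so the primary estimate is not fully determined in advance.

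2. **Design factors.** Randomising within clinic type removes differences between types from the treatment contrast. A clustered standard error from a model without type still counts those differences as noise. If types differ in abstinence, the standard error is larger than the design warrants and power is lost. The trial is planned at 80% power, so there is little to spare.

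The full covariate list could be left to an analysis plan that is not shown. But the article is not silent here: it states a selection rule and an a priori list. An analysis plan that followed them literally would inherit both features.

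**Working it through.** **Inputs from the protocol article (Power Analysis and Sample Size).** Control quit rate 3.72%, intervention 6.50%, ICC 0.01, about 36 patients per practitioner, 131 practitioners, type I error 0.05 (two-sided assumed), power 80%, attrition 20% of practitioners and 30% of patients, 2344 per arm.

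**Step 1: the plan's own figure.** Two proportions at 80% power need 984 per arm. The design effect is 1 + (36 − 1) × 0.01 = 1.35, and 984 × 1.35 = 1328. Dividing by 0.70 × 0.80 = 0.56 gives 2372, which is 1.2% above 2344. With a continuity correction (1055 per arm) and the retained cluster size 36 × 0.70 = 25.2 (design effect 1.242), 1055 × 1.242 / 0.56 = 2340. The stated figure therefore reproduces. It uses no strata or covariates, so the point does not alter it.

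**Step 2: expected analysis set.** 2344 × 0.56 = 1313 per arm. Expected events are 1313 × 0.0372 = 49 and 1313 × 0.065 = 85, about 134 in all.

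**Step 3: clinic type in or out of the model.** Simulation set-up:
- 102 practitioners (34 in each of 3 clinic types, 1:1 within type), 25 patients each.
- ICC 0.01 within type.
- Logit model with practitioner-clustered robust standard errors; 500 runs per scenario.
- True odds ratio 1.8, from (0.065/0.935) / (0.0372/0.9628) = 1.80.

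The document gives no quit rates by type, so the control rates are assumed.

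| Control rates by type | Power, type omitted | Power, type included | Mean SE, omitted | Mean SE, included | Type I error, omitted vs included |
|---|---|---|---|---|---|
| 3.7 / 3.7 / 3.7% | 79% | 79% | 0.207 | 0.206 | 4.8% vs 4.8% |
| 2.0 / 3.7 / 5.5% | 76% | 84% | 0.221 | 0.206 | 3.0% vs 4.6% |
| 1 / 3 / 7% | 67% | 81% | 0.250 | 0.210 | 3.4% vs 6.0% |

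Simulation error is about 2 points for power (√(0.8 × 0.2/500) = 0.018) and 1 point for type I error (√(0.05 × 0.95/500) = 0.010). In the last row the empirical SD of the estimate is 0.204 with type omitted, so a mean SE of 0.250 is too large. With type included the SD is 0.209 and the SE 0.210. The mean log odds ratio hardly moves: 0.585 omitted, 0.599 included. Clinic size was not simulated.

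**Step 4: how these spreads compare with the planned ICC.** Between-type variance divided by p(1 − p):
- 2.0/3.7/5.5%: mean 3.73%; 0.000204 / 0.0359 = 0.006.
- 1/3/7%: mean 3.67%; 0.000622 / 0.0353 = 0.018.

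The moderate spread could fit inside a total ICC of 0.01; the wide one could not.

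**Step 5: the screen.** With no treatment effect, 104 practitioners × 25 patients, and 10 assumed candidate covariates (4 truly prognostic) screened against outcome at p < 0.05, 300 runs chose 67 different covariate sets. Against a fixed model with the 4 prognostic covariates, the log odds ratio moved by an SD of about 0.015. Type I error was 5% for both models.

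**The case against.** The a priori list is not presented as the complete model. Baseline measures are added without being named, and an article commonly leaves the full list to an analysis plan. That stands in part: the article does not exclude clinic type, and the screen might bring it in. But nothing assures this, and the screening rule itself is stated outright.

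A reader might infer more than the document supports:

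- **That covariates are chosen after seeing outcomes.** The screen follows directly on the baseline comparison of arms and could mean covariate-by-arm comparisons, which need no outcome data. The text does not say which is meant.
- **That the planned standard error is too large in this trial.** Sites are randomised, but the model clusters on practitioners. Compensation Details pays NGO sites per participating practitioner, so a site may have several. Ignoring correlation within a site would make the standard error too small. The simulation has no site level, so the net direction is not established.
- **That a definite amount of power is lost.** Assumed rates of 2/4/9% add 0.018 to the ICC: 1 + 24.2 × 0.028 = 1.68, and 1313/1.68 = 782 per arm gives about 71% power against 83%. This treats 0.01 as the ICC within clinic type, which the article does not say. If 0.01 is the total, variation between types is already inside it; planned power does not fall, and adjustment only gains precision.
- **That the model would be unstable.** About 134 events support roughly a dozen covariates at 10 events each, and the article plans collinearity checks.
- **That screening materially distorts the estimate.** Step 5 shows otherwise for a mechanical rule, and SES, gender, age and baseline measures are fixed in any case.

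**Conclusion.** The point holds as a recommendation to improve a stated rule. Covariates are chosen partly by a bivariate screen with no candidate list or threshold, and the two randomisation factors are not named for the primary model.

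The consequence of omitting clinic type is lost precision and a conservative test, without material bias. Under the assumed rates the power difference is nil, about 8 points (76% vs 84%) or 14 points (67% vs 81%). This rests on the assumed quit rates, on an ICC of 0.01 within type, and on no correlation within sites beyond practitioner level. The actual size cannot be derived from the document and may be zero.

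The screen matters because it leaves room for analyst discretion, not because it is expected to shift the estimate or type I error appreciably.

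**What to change.** Replace the bivariate screen with one prespecified primary model: arm, clinic type, a coarse clinic-size category, SES, gender, age, and baseline tobacco measures listed by name. Do not use matched-set indicators: the number of sites is not given, and many indicators with about 134 expected events could leave sets with no events. Keep the comparison of arms at baseline descriptive. Put any model with further covariates in a sensitivity analysis. Keep the stratified analyses by clinic type as they are.

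The cost is wording only: clinic type and size are known from randomisation, and SES, gender and age are already planned adjustments. The model should be locked soon, because Results reports 188 six-month follow-ups completed by July 2024.
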